### Sample size calculation and statistical analyses

All quantitative data analyses will be conducted using R (61), RStudio (62), and MATLAB (60).

Due to the nested nature of group intervention data (63) and more specifically the scarcity of research regarding IPT in patients with cancer other than breast cancer, sample size calculations are to be treated with caution. A sample size of 40 participants is considered appropriate for this feasibility study.

Feasibility outcomes will be analyzed using percentages. Descriptive analyses of sociodemographic data will be conducted. Preliminary efficacy will be analyzed in within-subject comparisons for each outcome measure and reported with 95% confidence intervals (CI). Results regarding the primary outcome (symptoms of depression, PHQ-9) will be considered indicative of efficacy if the CI is above zero and includes the predefined Minimal Clinically Important Difference (MCID) of 5 points as previously determined by Löwe et al. (64). Results regarding secondary and tertiary outcomes will be considered indicative of efficacy if it is above zero.

Missing data will be reported as such. It is expected that at least a subset of dropouts may nevertheless be available to complete the post-treatment assessment, improving the accuracy of data collected. An interim analysis is not planned.

Qualitative analysis will be conducted using MAXQDA 2022 software (65). Record transcripts will undergo qualitative content analysis as described by Mayring (66) using deductive-inductive category formation, starting with an initial batch of 6 interviews. Iterative analysis will continue until saturation is reached. Procedures and results will be recorded and reported in accordance with the Standards for Reporting Qualitative Research (SRQR) (67). Saturation will be assessed using the 16-item checklist provided by Ahmed (68). Saturation will be defined as lack of emergence of new themes in three consecutive interview transcripts. Meta-analysis indicates a sample size of 13 is enough to reach saturation for most studies (69). Analysis will focus on the following aspects included in the semi-structured interview (**Table 4**): changes in everyday life, helpful elements of group IPT, inappropriate elements of group IPT, interpersonal experiences in group IPT, challenges in group IPT, support regarding challenges, adverse effects, barriers and facilitators for participation in group IPT and study procedures, and outlook.

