### Participant recruitment

Participants will be recruited from the pool of patients receiving treatment in oncological facilities of the University Hospital Tübingen (UKT), and the Comprehensive Cancer Center Tübingen-Stuttgart including the psychosocial counselling facilities (Krebsberatungsstelle Tübingen) using flyers, posters, social media outlets and information provided by nurses, doctors, and psychologists. Patients in in- and outpatient oncological care at the UKT complete an electronic psycho-oncological screening (ePOS) as part of routine cancer patient care and are approached by the psycho-oncology services if indicated (see 39, 40). If they indicate symptoms of depression (rating of 3 or higher on PHQ-9), psychological distress (rating of 4 or higher on DT analogue scale) on the ePOS, their psycho-oncologist will ask if they are interested in participating in the study. Participants who indicate interpersonal distress (i.e. “no” for “Do you have someone to talk to about your worries”, “yes” for “familial problems”) will also be informed about the program and will be included in the pilot study if they meet the inclusion criteria. Information about the treatment program and ways of referral will also be sent out to practitioners who might treat cancer patients (general practitioners, oncologists, gynecologists, urologists, neurologists, surgeries, etc.) in the area around the clinic. Questions regarding the study will be answered via email, phone or in person. Those seeking participation will be screened for inclusion and exclusion criteria. Participants will not receive compensation for participating in the study. Recruitment will end when 40 patients have completed assessments. For the qualitative study, recruitment will end when saturation is reached as described below.

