#### Intervention structure

The IPT intervention encompasses 10 weekly sessions of 60 minutes each. It is structured into modules incorporating IPT core themes: psychoeducation, role transitions (incorporating grief for the “lost healthy self”), and connection/interpersonal conflict. (**Table 2**) shows sessions, session content, therapeutic goals and patient homework for each module. Pre- and post-group treatment sessions will be held as described in (**Table 3**) (see 41). In pre-group treatment sessions, participants will set individual goals that fit within the IPT core themes and will be encouraged to work on them in group sessions by applying the session content to their specific examples (e.g. in role-play sessions). Post-group sessions will include a semi-structured interview encompassing questions on goal attainment, interpersonal experiences (42), outlook and change maintenance and questions regarding barriers and facilitators to participation and unintended effects of the intervention. Groups will consist of at least three and at most ten participants at a time and will remain in the same constellation across all ten group sessions.

**Table 2 T2:** Intervention modules description.

Session no.	IPT Problem Area	Content	Goals	Homework assignment
1	Psycho-education: cancer and mental health	• vulnerability-stress model • psychiatric comorbidities of cancer and “sick role” • resilience factors retained throughout cancer treatment • premises of IPT and application to struggles of patients with cancer	• Foster understanding of mental health issues in connection with cancer and treatment options • normalize distress/depression as a reaction to cancer diagnosis • empowerment • foster group coherence through shared experience of cancer diagnosis	• reflect strongest symptom of depression, apply coping/resilience as discussed
2	Role Transition: Introduction	• common role transitions for patients with cancer • transfer to individual role transitions • introduction to mindfulness exercises: 3-minute breathing space	• identify current changes and constants • reframe current changes as role transitions in wake of cancer diagnosis • normalize struggles adapting to change • foster group coherence by identifying shared struggles • foster reflection of individual, implicit connotations of new role	• reflect personal role transitions in wake of cancer diagnosis regarding three aspects: “what is lost?”, “what remains the same?”, “what is gained?”

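### The plan recognises that patients are nested in therapy groups, but its stated efficacy confidence intervals make no allowance for it

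*Protocol article*

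**What the plan says.** Under Intervention structure, the protocol article sets the treatment units: "Groups will consist of at least three and at most ten participants at a time", and these "will remain in the same constellation across all ten group sessions". Under Participant recruitment, "Recruitment will end when 40 patients have completed assessments".

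Under Sample size calculation and statistical analyses, the nesting appears once, as a reason for caution about sample size calculations: "Due to the nested nature of group intervention data (63"). The same paragraph then says "A sample size of 40 participants is considered appropriate for this feasibility study". No ICC, standard deviation, power or effect size is given.

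The efficacy analysis follows in the same section: "Preliminary efficacy will be analyzed in within-subject comparisons for each outcome measure and reported with 95% confidence intervals (CI"). The primary result, on the PHQ-9, "will be considered indicative of efficacy if the CI is above zero and includes the predefined Minimal Clinically Important Difference (MCID) of 5 points". Secondary and tertiary outcomes need only an interval above zero. No group term, cluster-robust variance or ICC is mentioned anywhere in the article.

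**The concern.** Patients who spend ten sessions in the same closed group share therapists, group climate and each other's feedback. The article's introduction counts on this: it expects the group itself to relieve burden and create connection. Some positive correlation of change within groups is therefore plausible, though the documents do not quantify it.

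The article goes beyond leaving a detail open. It fixes the comparison, the interval and the decision rules, and it uses the nesting only for sample size. An analyst who follows the stated sentence has no prompt to bring therapy group into the variance. Seven scores (PHQ-9, GAD-7, Distress Thermometer, R-UCLA, BS6 and the two INQ constructs) at two time points give 7 × 2 = 14 verdicts that rest on this variance. Twelve of them depend on the above-zero condition alone.

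An analysis without a group term also gives no estimate of between-group variation. The planned larger trial needs one, and Objectives and research questions says that all data collected will inform progression to it.

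**Working it through.** **Inputs from the protocol article.** N = 40; group size m from 3 to 10; 95% intervals, taken as two-sided; PHQ-9 threshold of 5 points. Number of groups: 40/10 = 4, up to 40/3 ≈ 13. The sample size of 40 cannot be reproduced, because no calculation stands behind it.

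**Assumptions.** ICC of change scores 0.02 to 0.10; SD of PHQ-9 change 5 points; equal groups; normal data; an analysis that ignores group (a paired t interval); reduction in symptoms counted as positive.

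**Step 1: design effect.** DE = 1 + (m − 1) × ICC. The correct standard error is the plain one times √DE. For m = 8 and ICC 0.10: 1 + 7 × 0.10 = 1.70, √1.70 = 1.30, effective n = 40/1.70 = 23.5.

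**Step 2: true coverage of the nominal 95% plain interval** (simulation, 40,000 trials per setting; repeat runs agree within about half a percentage point).

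| Layout | ICC | DE | Coverage |
|---|---|---|---|
| 13 groups of 3 | 0.02 | 1.04 | 94.6% |
| | 0.05 | 1.10 | 93.9% |
| | 0.10 | 1.20 | 92.9% |
| 5 groups of 8 | 0.02 | 1.14 | 93.5% |
| | 0.05 | 1.35 | 90.9% |
| | 0.10 | 1.70 | 86.8% |
| 4 groups of 10 | 0.02 | 1.18 | 93.0% |
| | 0.05 | 1.45 | 90.0% |
| | 0.10 | 1.90 | 84.4% |

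At ICC 0 coverage is 95% in every layout. A t interval on the group means covers about 95% throughout.

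**Step 3: false above-zero verdicts when the true change is zero.** Half of the non-coverage falls on each side. At ICC 0.10 the rate is (100 − 86.8)/2 = 6.6% with 5 groups of 8 and (100 − 84.4)/2 = 7.8% with 4 groups of 10, against a nominal 2.5%.

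**Step 4: half-width in PHQ-9 points, 5 groups of 8.**

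- Plain: t(0.975, 39) × SD/√N = 2.023 × 5/√40 = 1.60.
- Clustering alone: 1.60 × √1.14 = 1.71 at ICC 0.02 and 1.60 × √1.70 = 2.09 at ICC 0.10.
- Group-mean t interval with 4 degrees of freedom: 2.20 at ICC 0.02, 2.40 at 0.05 and 2.69 at 0.10. At ICC 0 it is already 2.776 × 0.940 × 5/√40 = 2.06, where 0.940 is the mean ratio of sample to true SD for five values. Much of its extra width is thus the price of having only five groups.

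**Step 5: effect on the PHQ-9 rule.** With half-width h, the estimate must exceed h and lie within 5 ± h. At h = 1.6 the passing range is 3.4 to 6.6. At h = 2.1 it is 2.9 to 7.1. Here the condition of including 5 binds, and widening the interval makes the combined rule easier to meet. The above-zero condition starts to bind only when h exceeds 2.5, because 5 − h is then smaller than h.

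**The case against.** The strongest objection is that the article names no test, model or variance estimator. A mixed model with a group effect is also a within-subject comparison and would satisfy the quoted sentence. The article condenses a fuller plan that is not shown, and citing a source on nesting suggests awareness of the problem. This stands in part. A reader might infer that the plan specifies a paired t test, or treats the 40 change scores as independent; the document says neither. What remains is that the article states its analysis and decision rules, raises nesting, and carries it only into sample size.

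A reader might also infer that every efficacy interval is too narrow. That would need a positive ICC of change for each outcome, and the documents give none. With groups of three the loss is about two percentage points even at ICC 0.10. The serious figures need both large groups and the upper end of the assumed range.

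It is tempting, too, to say that the half-width ought to be 2.2 to 2.7 points instead of 1.6. That range mixes clustering with the loss of degrees of freedom of one particular method.

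Finally, this is a feasibility study. Under Feasibility outcomes, adherence is the primary progression criterion, and no stated go or stop threshold uses these intervals. Efficacy is labelled preliminary, and the Discussion concedes the lack of a control group. This stands and lowers the severity. An ICC from 4 to 13 groups will also be imprecise, but an imprecise estimate with its interval is more use to the larger trial than none.

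**Conclusion.** The point holds in conditional form. The plan acknowledges nesting but states no allowance for it in the efficacy intervals. If therapy group is ignored and changes correlate positively within groups, those intervals are too narrow: slightly with groups of three, and materially with groups of 8 to 10 at an ICC of 0.05 or more. With an assumed SD of change of 5 points and groups of 8, clustering alone takes the half-width from 1.6 to about 1.7 to 2.1 points.

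The direction differs by outcome. For secondary and tertiary outcomes the above-zero rule is met too often. For the PHQ-9 the two conditions pull in opposite directions, so the net effect depends on the estimate and the SD.

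All sizes rest on the assumed ICC and SD; the group sizes and N come from the article. Severity is moderate.

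**What to change.** Amend the efficacy sentence under Sample size calculation and statistical analyses along these lines: change from T0 in each outcome will be estimated in a linear mixed model with time as fixed effect and random effects for participant and for therapy group, including a random group effect on change, with Satterthwaite or Kenward-Roger degrees of freedom.

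Add two provisions:

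- If the group variance is estimated at zero, which can happen with so few groups, report as sensitivity analysis the intervals inflated by √DE for ICC 0.02, 0.05 and 0.10.
- Report the ICC of change with its confidence interval, for planning the larger trial.

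The cost is small: a group identifier, a few lines in R (already the named software), and no extra data from patients. Trial status gives six participants as of 10/24, so as of that date the amendment could precede almost all outcome data. The price is wider intervals and an ICC that will itself be imprecise.

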Primary outcome will be symptoms of depression at completion of the treatment and 3-months follow-up, which will be assessed using the Patient Health Questionnaire (PHQ-9). As secondary outcomes we chose symptoms of anxiety, which will be assessed using the Generalized Anxiety Disorder Questionnaire (GAD-7), and psychological distress as measured by the Distress Thermometer (DT) at completion of the treatment and 3-months follow-up. Tertiary measures are self-reports of loneliness as measured by the R-ULCA Loneliness Scale, perceived social support as measured by the Brief Social Support Scale (BS6), interpersonal needs (perceived burdensomeness and thwarted belongingness) as measured by the Interpersonal Needs Questionnaire (INQ) at completion of the treatment and 3-months follow-up.

Qualitative data will consist of the audio recording of the post-intervention semi-structured interviews. Records will be saved using the patient pseudonym on study tablets that are not connected to the internet and will be transcribed by the study team. Recordings will be deleted after analysis is completed. A translation of the interview guidelines can be seen in (**Table 4**).

**Table 4 T4:** Post-intervention semi-structured interview.

Topic	Question
Goal achievement and relevance to everyday life	In the preparatory session, you formulated the following goal for the group therapy: X What has changed in relation to X since the start of therapy? How do you notice the change in everyday life? What would you say - have you achieved, partially achieved or not achieved the goal? Which aspects of the group therapy did you find helpful regarding X? Which aspects did you find inappropriate or not useful? Have there been any changes in your everyday life beyond the goals we just talked about? How do you observe these changes? How is the change related to the group therapy? What interpersonal experiences do you take away from the group?
Challenges and adverse effects	What were the particular challenges or difficulties for you in group therapy? How did the therapists or the group support you in overcoming the challenges? (How could the therapists or the group have supported you better in overcoming the challenges?) Did group participation have adverse effects for you?

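### The PHQ-9 efficacy rule requires the confidence interval to contain 5 points, so an interval lying wholly above the MCID fails it

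*Protocol article*

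**What the plan says.** The section on sample size and statistical analyses in the protocol article sets out the efficacy analysis: "Preliminary efficacy will be analyzed in within-subject comparisons for each outcome measure", with 95% confidence intervals. For the primary outcome, the PHQ-9, the result "will be considered indicative of efficacy if the CI is above zero and includes the predefined Minimal Clinically Important Difference (MCID) of 5 points".

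The next sentence sets a different rule for the other outcomes: "Results regarding secondary and tertiary outcomes will be considered indicative of efficacy if it is above zero". The requirement to contain a particular value therefore applies to the primary outcome alone.

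On size, the same section says "A sample size of 40 participants is considered appropriate for this feasibility study", and the recruitment section says "Recruitment will end when 40 patients have completed assessments". Neither gives an SD, an expected effect or a power.

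The section on feasibility outcomes makes participant adherence the primary progression criterion, with go, amend and stop bands divided at 80% and 40%. The objectives say that all data collected will inform the decision on a full trial.

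**The concern.** The primary rule joins two conditions: the interval must exclude zero, and it must contain 5. The second condition sets a ceiling as well as a floor. If the treatment works so well that even the lower limit exceeds the clinically important difference, the interval no longer contains 5 and the rule withholds the label.

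Containing a fixed value is also easier for a wide interval than for a narrow one. Over part of the range, the rule therefore favours noisier data.

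This is the only stated success criterion for the primary outcome, and preliminary efficacy is a declared aim. Applied literally, it could report a large improvement as not indicative of efficacy. If instead it is reinterpreted once results are known, it is no longer a predefined criterion.

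**Working it through.** **The wording alone.** Let d be the observed mean PHQ-9 reduction (baseline minus follow-up) and h the half-width of the 95% interval. The rule passes when 0 < d − h ≤ 5 ≤ d + h, that is, when |d − 5| ≤ h and d > h. An interval of 5.4 to 8.6 has a lower limit above 5 and fails. This needs no assumption about the SD. It also follows that an observed mean of 2.5 or less can never pass, because d > h ≥ 5 − d requires d > 2.5.

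**Inputs for the size.** From the article: n = 40, MCID 5, 95% interval (taken as two-sided), within-subject change. Assumed, because the article does not give it: SD of change, shown over 4 to 7 points. Changes are taken as normal, and clustering by therapy group is ignored. The article states no operating characteristics for the rule, so there is no figure of its own to reproduce.

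**Half-width and passing window at n = 40.** h = t(0.975, 39) × SD/√40, with t = 2.023. For SD 5, h = 2.023 × 5/6.325 = 1.60, and the window is 5 ± 1.60.

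| SD | h | observed mean reductions that pass |
|---|---|---|
| 4 | 1.28 | 3.72 to 6.28 |
| 5 | 1.60 | 3.40 to 6.60 |
| 6 | 1.92 | 3.08 to 6.92 |
| 7 | 2.24 | 2.76 to 7.24 |

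With SD 5, an observed reduction of 8 gives 6.40 to 9.60 and fails. An observed reduction of 3.5 gives 1.90 to 5.10 and passes.

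**Probability of passing at n = 40** (simulation, 200,000 draws per cell, SD estimated in each draw):

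| true reduction | 3 | 4 | 5 | 6 | 7 | 8 |
|---|---|---|---|---|---|---|
| SD 4 | 0.13 | 0.66 | 0.95 | 0.66 | 0.13 | 0.004 |
| SD 5 | 0.31 | 0.77 | 0.95 | 0.77 | 0.31 | 0.04 |
| SD 6 | 0.46 | 0.82 | 0.95 | 0.82 | 0.46 | 0.13 |
| SD 7 | 0.57 | 0.85 | 0.95 | 0.86 | 0.58 | 0.25 |

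Each row is almost symmetric about 5, so a benefit 2 points above the MCID fares no better than one 2 points below it. Reading down the columns for 3 and 7, raising the SD from 4 to 7 raises the chance of passing from 0.13 to 0.57 or 0.58.

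**Dependence on n, SD 5:**

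| n | 10 | 20 | 40 | 80 | 160 |
|---|---|---|---|---|---|
| true 3 | 0.38 | 0.55 | 0.31 | 0.06 | 0.001 |
| true 5 | 0.77 | 0.94 | 0.95 | 0.95 | 0.95 |
| true 7 | 0.77 | 0.61 | 0.31 | 0.06 | 0.001 |

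At a true change of 7, fewer patients means a higher chance of passing throughout the table. At 3 this reverses between n = 20 and n = 10, and at 5 imprecision only lowers the chance, because a very wide interval fails to exclude zero.

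**Alternative rules, n = 40, SD 5:**

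| true reduction | 3 | 4 | 5 | 6 | 7 | 8 |
|---|---|---|---|---|---|---|
| lower > 0 and upper ≥ 5 | 0.31 | 0.77 | 0.975 | 0.999 | 1.00 | 1.00 |
| lower > 0 and point estimate ≥ 5 | 0.006 | 0.10 | 0.50 | 0.90 | 0.99 | 1.00 |
| lower ≥ 5 | 0.000 | 0.001 | 0.025 | 0.23 | 0.69 | 0.96 |

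All three rise steadily with benefit. The first matches the written rule below 5, so it keeps the reward for imprecision there. The second largely removes it: at a true change of 3, raising the SD from 4 to 7 moves it only from 0.001 to 0.036.

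**The case against.** The sponsor probably meant that the interval should reach or exceed 5, and the interval itself will be published, so any reader could see a result such as 5.4 to 8.6 for what it is. That is fair as far as intent goes, but nothing in the article says it, and a predefined criterion has to be right as written.

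The probabilities rest on an assumed SD, and nothing in the article shows that true reductions of 7 or 8 points are likely. This stands: the percentages illustrate the rule and are not properties of this trial. The failure of an interval wholly above 5 does not depend on them.

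Three stronger readings are tempting and are not supported.

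- A reader might infer that less precise data always pass more easily. They do not: the above-zero condition reverses the effect for very wide intervals, as the rows for true changes of 3 and 5 show. Recruitment is also planned to run to 40 completed assessments, so n = 10 is hypothetical.
- A reader might infer that the rule could wrongly block the full trial. The article makes adherence the primary progression criterion. The PHQ-9 rule informs that decision and does not gate it.
- A reader might count it as a further fault that "Primary outcome will be symptoms of depression at completion of the treatment and 3-months follow-up" names two time points without saying how they combine. That detail is commonly left to an analysis plan, which is not shown. Choosing a single time point or adding a responder proportion would be a preference, not a correction.

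**Conclusion.** The point holds as a defect in a stated rule. By its wording, a PHQ-9 interval lying wholly above 5 is not indicative of efficacy, and no other part of the article repairs this.

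With n = 40 and an assumed SD of 5, a true 8-point reduction would earn the label about 4% of the time (0.4% to 25% over SD 4 to 7). True reductions of 3 and 7 would each earn it 31% of the time. The reward for imprecision is real around n = 40 when the true change differs from 5, but it is bounded by the above-zero condition. These figures assume normal changes and no clustering by group.

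The consequence is a potentially misleading statement about preliminary efficacy, not a wrong automatic decision on progression. The rule should still be corrected, because rewording it costs almost nothing.

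**What to change.** Define PHQ-9 change as the T0 score minus the follow-up score, so that a positive value is an improvement, and replace the rule with: *The result is considered indicative of efficacy if the lower 95% limit of the mean PHQ-9 reduction is above 0 and the point estimate is at least 5. A clinically important change is shown if the lower limit is at least 5.* A larger benefit then cannot fail, and a wide interval is no longer enough to bring in a small effect.

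At minimum, change the condition to *includes or lies entirely above* 5. That cures the failure of the strongest results but leaves the reward for imprecision below 5 as it is (true 3, SD 5, n = 40: 31% either way).

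The cost is the wording of one rule, with no new data and no change to the sample. The trade-off is that the point-estimate version is stricter for true changes below 5: at a true change of 4, SD 5 and n = 40, it passes 10% of the time instead of 77%. The trial status section reports 6 participants as of 10/24. The change should be made and dated before outcomes are analysed.

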### Outcome measures

#### Feasibility outcomes

Feasibility measures will include recruitment rates and adherence to treatment, suitability of criteria for exclusion and inclusion, suitability of data collection procedures, and suitability of recruitment procedures. Participant flow will be documented according to CONSORT guidelines (38). Challenges in trial organization and changes to amend difficulties will be documented in the study teams meeting protocols. Therapists’ adherence to the intervention manual will be documented using supervision session protocols and the IPT scale of Strategies in Therapy Use Form – Therapist Version (STUF) developed by Swartz et al. (43). Documentation of reasons for drop-out and documentation of the post-intervention session will provide information on previously disregarded patient reported outcomes, suitability of study procedures according to the participants, and unintended effects of the intervention.

Participant adherence to treatment will be used as primary criterion for trial progression, with an adherence rate above 80% indicating progression (‘Green/Go’), an adherence rate between 80% and 40% indicating progression only after thorough revision and amendment (‘Amber/amend’) and an adherence rate below 40% indicating no progression (‘Red/stop’) (44). Status regarding the progression of the trial will be assessed regularly in the study teams meetings and documented in meeting protocols, along with changes to the protocol that might be implemented to amend adherence rates. Qualitative data will be used to inform amendments to study procedure and intervention structure or content.

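### The saturation rule sets no minimum number of therapy groups, so all content-analysed transcripts could come from one closed group

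*Protocol article*

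**What the plan says.** The protocol article fixes the qualitative sample by a stopping rule, not by a number. Under Sample size calculation and statistical analyses, content analysis proceeds "starting with an initial batch of 6 interviews" and continues iteratively until saturation. The definition follows: "Saturation will be defined as lack of emergence of new themes in three consecutive interview transcripts". The same paragraph names a 16-item checklist for assessing saturation and cites a meta-analysis in which 13 interviews were enough for most studies.

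Participant recruitment attaches a consequence: "For the qualitative study, recruitment will end when saturation is reached as described below". The quantitative part runs on separately until 40 patients have completed assessments.

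Intervention structure sets group size at 3 to 10 and says that groups "will remain in the same constellation across all ten group sessions". It also places the semi-structured interview in the individual post-group session, which Session structure makes mandatory. Feasibility outcomes adds a use for the material: "Qualitative data will be used to inform amendments to study procedure and intervention structure or content".

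No section says how many groups the transcripts must cover, in what order they are read, or whether the three transcripts without new themes may belong to the first six.

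**The concern.** Interviews in this study become available in blocks. A closed group finishes its ten sessions together, and its members then have their post-group interviews. Much of the interview guide (Table 4) concerns things that members of one group have in common: what interpersonal experiences they take from the group, how the therapists or the group helped with difficulties, and how the organisation worked. Repetition among members of the same group is therefore to be expected. It is weak evidence that a different group would raise nothing new.

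The article recognises nesting in group intervention data where it discusses the sample size of 40. It does not carry the thought over to the saturation rule a few lines later.

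At stake is the reach of the qualitative findings. Identifying barriers and facilitators is a stated objective, and all data are to inform the decision on a full trial. If the recorded and coded material came from one group, those findings would describe that group, while the report would say that saturation had been reached.

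**Working it through.** The plan gives no formula-based qualitative sample size to reproduce, so the check is a count.

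**Inputs from the article.** First batch 6; run of transcripts without new themes 3; cited benchmark 13 (all from Sample size calculation and statistical analyses). Group size 3 to 10 (Intervention structure). Pilot size 40 (Participant recruitment).

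**Earliest stop.** The text allows two readings.
- The three transcripts must follow the batch: 6 + 3 = 9.
- The last three of the batch may count: 6.

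**Fewest groups covered** = transcripts ÷ group size, rounded up:

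| Group size | 6 transcripts | 9 transcripts | 13 transcripts |
|---|---|---|---|
| 3 | 2 | 3 | 5 |
| 4 | 2 | 3 | 4 |
| 5 | 2 | 2 | 3 |
| 6 | 1 | 2 | 3 |
| 7 | 1 | 2 | 2 |
| 8 | 1 | 2 | 2 |
| 9 | 1 | 1 | 2 |
| 10 | 1 | 1 | 2 |

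A one-group stop is thus possible at 2 of the 8 permitted sizes on the first reading and at 5 of the 8 on the second. At 13 transcripts it is impossible at every size.

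**What would be left out.** Forty patients make at least 40 / 10 = 4 groups, and about 13 at size 3 (40 / 3 = 13.3). A one-group stop would leave at least 4 − 1 = 3 groups without content analysis.

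**How easily 9 transcripts arise in a group of 10.** Let c be the chance that a member is interviewed and recorded. The article gives no value, so c is an assumption. P(at least 9 of 10) = 10c⁹(1 − c) + c¹⁰. This is 0.38 at c = 0.8 and 0.74 at c = 0.9. For a group of 9, all must be recorded: c⁹ = 0.13 and 0.39. These are chances of having enough transcripts. The rule also needs three in a row without a new theme.

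**What is missed at 9 compared with 13.** For a theme held by a share p of patients (assumed) and independent interviews, P(missed) = (1 − p)ⁿ.
- p = 0.10: 0.39 at n = 9, 0.25 at n = 13.
- p = 0.20: 0.13 at n = 9, 0.06 at n = 13.

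Clustering of themes by group would raise these figures. In the limiting case, where a theme is either common to a whole group or absent from it, more interviews in the same group do not help. If half of the groups carry such a theme (assumed), one group misses it with probability 0.50 and two groups with 0.50² = 0.25. In that case the number of groups matters, not the number of transcripts.

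**The case against.** The strongest reply is that this is an edge case in a secondary part of a feasibility study, and that other sources cover the objectives. Much of that stands.

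- **Interviewing does not end.** A reader might infer from the recruitment sentence that later groups go unheard. The documents do not support that. The post-group session with its interview is mandatory, and Feasibility outcomes uses its documentation and the recorded reasons for drop-out. Table 1 also schedules acceptability and feasibility items at T1. What can close is the recorded, content-analysed set.
- **A one-group stop is not the usual course.** On the 6 + 3 reading it needs a group of 9 or 10 with nearly everyone recorded. Groups of 3 or 4 already force three groups.
- **Thirteen is not a floor.** It is cited as enough for most studies, so stopping at 9 does not contradict the article.
- **No objective is set by cancer type or stage.** Mixed types and stages are a feature of group composition, and one group may itself be mixed. The objectives do not call for acceptability by type or stage.
- **Nor is it stated that interviews must show whether an amendment worked.** Protocol changes aimed at adherence are allowed during the study, but the sentence on amendments informed by qualitative data gives no timing.
- **The checklist may help.** Its content is not in the document, so whether it asks about the spread of sources cannot be judged.

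It can also be said that an article leaves the selection of transcripts to the full protocol. That is fair for ordering details. But the article states the stopping criterion and its consequence outright, and that criterion is satisfied by transcripts from a single group. This part of the concern remains.

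**Conclusion.** The point holds in a limited form. As written, the saturation rule can be met by 9 transcripts from one group of 9 or 10, or by 6 from one group of 6 to 10 if the three may fall within the first batch. At least 3 further groups would then be interviewed but not content-analysed. Because the interview asks about experiences that a group shares, an absence of new themes within one group does not establish saturation for the programme.

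The counts rest only on figures in the article. The probabilities are illustrations that depend on assumed recording rates and theme frequencies. This is a weakness in a stated stopping rule that is cheap to repair. It is not an internal contradiction, and it does not affect the progression criterion, which is adherence.

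**What to change.** Keep the three-transcript criterion and add two conditions under Sample size calculation and statistical analyses:

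1. The three consecutive transcripts without new themes come from at least two different groups. State the reading order; alternating between groups makes this easy to meet.
2. Saturation is not declared before 13 interviews have been analysed, which turns the cited benchmark into a minimum.

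If procedures or the intervention are amended during the pilot, transcripts from at least one later group should be included where one exists. The sentence on ending qualitative recruitment should refer to these conditions.

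The cost is recording, transcribing and coding a few more interviews that are held anyway: at the earliest possible stop, 13 − 9 = 4 more, or 13 − 6 = 7 more on the looser reading. The two-group condition or an amendment could add some. The pilot should not need to be longer, since 40 patients already require at least 4 groups. The timing is favourable: according to Ethics and dissemination, qualitative collection had not yet been approved and would not start before approval, and Trial status reports 6 patients recruited.
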